### Participant Withdrawal

Participants can withdraw from the study for any reason at any time if they wish to do so, without any consequences. The investigator can decide to withdraw a participant from the study for urgent medical reasons.

### Outcome Measures

The study design and variables at each time point are presented in Figure 2. The primary outcome is periprocedural anxiety at T3 (State-Trait Anxiety Inventory for Children [STAI-C] and Visual Analog Scale [VAS]). Secondary outcomes include preprocedural anxiety (VAS and STAI-C), user experience, child behavioral and emotional problems (Child Behavioral Checklist [CBCL]), and parental anxiety (State-Trait Anxiety Inventory [STAI]).

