### Sample Size

To conduct analysis of covariance (ANCOVA) on the level of periprocedural anxiety at time point (T) 3 (primary outcome) with a Cohen *d* of 0.5, an α of .05 (2-tailed), and a power of .80, a sample size of 128 patients is needed (64 patients per group). Based on earlier studies, we anticipate finding a medium effect size [16].

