#### Child Anxiety

The anxiety level of participants is measured before and after the MRI scan (T2 and T3) with the STAI-C, a questionnaire where parents and children evaluate statements on a scale from 0 (not at all) to 4 (completely true). The STAI-C is a widely used and validated self-report instrument for measuring state and trait anxiety [24]. The STAI-C has a good-to-excellent interobserver and intraobserver reliability and was validated in Dutch [25]. The VAS will be used to assess the child’s anxiety level by the child himself, the parents, and the medical staff. The VAS shows 6 faces in order from not scared at all (most left face) to extremely scared (most right face; see Figure 3) [26]. The participants select the expression that fits their feeling before and after the MRI scan (T2 and T3). Because of the nonverbal character and the simplicity, this instrument offers a quick and reliable assessment that can be used in different settings [27,28]. The VAS is a widely used and studied instrument, has been shown to have a good reliability and validity, and is validated in Dutch [29]. The medical staff who accompanied the child were instructed to observe the anxiety of the child before the procedure in the MRI room and during the MRI scan (T2 and T3) by using the VAS [30].

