#### Primary Study Parameter(s)

To test the efficacy of the VR intervention, we will compare the VR group to the CAU group with an ANCOVA. The primary outcome variable is the child’s situational anxiety during MRI scan (T3; VAS child, continuous score), corrected for age, sex, baseline anxiety, and CBCL scores as well as type of MRI. In case of nonnormality, we will perform a Mann-Whitney *U* test.

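### The article defines the primary outcome in two ways: STAI-C and VAS at T3 in one section, the child-rated VAS at T3 alone in another

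*Protocol article*

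**What the plan says.** Two sections of the protocol article define the primary outcome.

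- Outcome Measures: "The primary outcome is periprocedural anxiety at T3 (State-Trait Anxiety Inventory for Children [STAI-C] and Visual Analog Scale [VAS"]). This names two instruments, with no rater, no ranking and no rule for combining them.
- Statistical Analysis, Primary Study Parameter(s): "The primary outcome variable is the child’s situational anxiety during MRI scan (T3; VAS child, continuous score"). This names one instrument, one rater and one time point, to be tested by ANCOVA.

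Other sections bear on the point without settling it.

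- Abstract and Introduction: the primary outcome is the child's procedural or periprocedural anxiety; no instrument is named.
- Sample Size: the calculation is for an ANCOVA "on the level of periprocedural anxiety at time point (T) 3 (primary outcome"), with Cohen d of 0.5, "an α of .05 (2-tailed), and a power of .80", giving 128 children. No instrument is named here either.
- Child Anxiety: the VAS records the child's "anxiety level by the child himself, the parents, and the medical staff". The STAI-C is completed by parents and children. Both instruments are used at T2 and T3.
- Secondary outcomes: Outcome Measures lists STAI-C and VAS as secondary only for preprocedural anxiety. Secondary Study Parameter(s) names child anxiety at T2 and parental anxiety as the main secondary outcomes. T3 child anxiety reappears only in an exploratory regression, with no instrument given.

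**The concern.** Both definitions stand in the current text, and they cannot both be the primary outcome. T3 STAI-C is primary in one section, absent from the primary analysis in another, and not a named secondary outcome anywhere. A reader cannot tell whether a T3 STAI-C result is confirmatory.

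The discordant case shows what is at stake. Suppose the child VAS at T3 shows no difference and the T3 STAI-C favours VR. Under the analysis section the trial is negative. Under Outcome Measures the STAI-C result could be reported as a primary finding. With a single alpha and no stated rule linking the two instruments, that choice could be made after the results are known.

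**Working it through.** **Inputs from the article (Sample Size, Study Design).** d = 0.5, two-sided alpha 0.05, power 0.80, 64 per arm, 1:1 allocation.

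**Assumed input.** The correlation r between the two T3 test statistics. The article gives none, so results are shown from 0 to 0.9.

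**Step 1: reproduce the stated sample size.**
Normal approximation: n per arm = 2(1.960 + 0.842)² / 0.5² = 62.8, so 63 per arm, 126 in total.
Two-sample t-test (noncentral t): 63.77, so 64 per arm, 128 in total, as stated. Power at 64 per arm is 80.1%.
The stated figure is therefore that of one two-sided 5% test.

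**Step 2: two primaries, either one sufficient at 5%.**
Familywise error = 1 − P(|Z₁| < 1.96 and |Z₂| < 1.96), with Z₁ and Z₂ bivariate standard normal with correlation r. At r = 0 this is 1 − 0.95² = 9.75%.

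**Step 3: two primaries, both required, d = 0.5 on each.**
Expected Z = 0.5 / √(2/64) = 2.828, and 2.828 − 1.960 = 0.868. One test has power Φ(0.868) = 80.7% by the normal approximation. Joint power is the bivariate normal probability that both standardised deviations lie below 0.868. At r = 0 this is 0.807² = 65.2%.

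| r (assumed) | Either sufficient: familywise error | Both required: joint power at 64 per arm |
|---|---|---|
| 0 | 9.8% | 65.2% |
| 0.3 | 9.5% | 67.7% |
| 0.5 | 9.1% | 69.7% |
| 0.7 | 8.3% | 72.2% |
| 0.9 | 7.0% | 75.9% |

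Counting only false positives that favour VR, the either-sufficient error is 4.9% at r = 0 and 3.5% at r = 0.9, against 2.5% for one test.

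**Step 4: compare with the plan.** Over the range shown, neither two-primary reading keeps both the stated 5% and the stated 80%. The single-outcome reading keeps both.

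**The case against.** The strongest reply is that the analysis section is the operative text. It is the only place that specifies a primary test, and it plans one ANCOVA on one variable from one rater. The sample size is for one test, and no primary test of T3 STAI-C is described. On this view Outcome Measures merely lists the instruments for a construct and sets no success rule.

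Much of this stands, and it limits what can be claimed. A reader might infer that the trial has two routes to a positive result at 5% each, so that the stated alpha fails. The article nowhere says that either instrument suffices. Its wording joins the two with *and*, which could equally mean that both must succeed; the harm would then be lost power, not excess false positives.

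A reader might also multiply raters by instruments (three for the VAS, two for the STAI-C) and treat five T3 scores as primary. The documents do not support that. The Child Anxiety section describes the parent and staff ratings as measurements and gives them no primary status, and the analysis section names the child as rater.

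The reply does not remove the contradiction. Outcome Measures labels STAI-C at T3 as primary in plain terms, and no other section gives it a different status. Nor is this a detail left to a fuller document: the article prints both definitions itself.

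**Conclusion.** The point holds as an internal contradiction, wrong as written; it is not a debatable design choice. The article does not fix which T3 result decides the trial, and this needs correcting before analysis.

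The size is conditional. If either instrument were sufficient at 5%, familywise error would be about 9%, and it is above 5% at every correlation shown. If both were required with d = 0.5 on each, alpha would hold and power would fall short of the planned 80% by roughly 4 to 15 percentage points (80 − 76 and 80 − 65). These figures rest on assumed correlations, on a normal approximation, and on no gain from covariate adjustment; the stated 128 is likewise reproduced without any such gain. The text does not say which case applies, so neither figure is the trial's actual error rate or power.

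The sample size itself is not wrong: it is right for a single primary outcome.

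**What to change.** Change the sentence in Outcome Measures so that the primary outcome is child-reported VAS anxiety at T3. List T3 STAI-C and the parent and staff VAS at T3 as secondary outcomes. This matches the analysis section and the single-test sample size.

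Make the change as a dated clarification before any outcome is compared by group. The Results section expects recruitment to end in December 2022 and analysis in 2023, so timing matters. Check the wording against the registered primary outcome, which is not shown here; if the registry names something else, the difference must be explained openly. Check also whether the Protocol Amendments section requires a formal amendment.

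Cost: N stays 128, type I error stays 5% and data collection is unchanged. STAI-C can no longer carry a primary claim.

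Keeping both instruments as primary would cost more:

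- Either sufficient, 0.025 each (Bonferroni): power per test at 64 per arm falls to 71.2%, and 80% needs 78 per arm, 156 in total.
- Both required: 80% joint power needs about 83 per arm at r = 0 (166 in total) to 71 per arm at r = 0.9 (142 in total).

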**Figure 2 figure2:**
[figure not shown]
Flow chart of the study design with the instruments at each time point. CBCL: Child Behavioral Checklist; MRI: magnetic resonance imaging; STAI: State-Trait Anxiety Inventory; STAI-C: State-Trait Anxiety Inventory for Children; T: time point; VAS: Visual Analog Scale; VR: virtual reality.

#### Background Variables

The following background variables will be collected: age, gender, and socioeconomic status (SES). Age and gender will be collected from the electronic record. SES will be based on a child’s postal code.

#### Child Anxiety

The anxiety level of participants is measured before and after the MRI scan (T2 and T3) with the STAI-C, a questionnaire where parents and children evaluate statements on a scale from 0 (not at all) to 4 (completely true). The STAI-C is a widely used and validated self-report instrument for measuring state and trait anxiety [24]. The STAI-C has a good-to-excellent interobserver and intraobserver reliability and was validated in Dutch [25]. The VAS will be used to assess the child’s anxiety level by the child himself, the parents, and the medical staff. The VAS shows 6 faces in order from not scared at all (most left face) to extremely scared (most right face; see Figure 3) [26]. The participants select the expression that fits their feeling before and after the MRI scan (T2 and T3). Because of the nonverbal character and the simplicity, this instrument offers a quick and reliable assessment that can be used in different settings [27,28]. The VAS is a widely used and studied instrument, has been shown to have a good reliability and validity, and is validated in Dutch [29]. The medical staff who accompanied the child were instructed to observe the anxiety of the child before the procedure in the MRI room and during the MRI scan (T2 and T3) by using the VAS [30].

**Figure 3 figure3:**

The Visual Analogue Scale (VAS) with faces from not anxious (most left) to extremely anxious (most right).

#### Child Behavior Problems

In the weeks before the MRI scan (T1), the parents/guardians complete the CBCL to examine behavioral or emotional problems in the last 6 months. The version used for children between the age of 6-18 years consists of 113 items, has been proven valid and reliable, and is validated in Dutch [31]. The respondent evaluates each item as not true (0), a bit/sometimes (1), or obviously/often (2). An internalizing problem and externalizing problem scale can be calculated.

#### Parental Anxiety

Parents/guardians rate their own feelings of anxiety with the STAI at T2 and T3. This self-report instrument contains 2 separate scales for trait and anxiety, combined into 40 items that the respondent rates as not at all (0), somewhat (1), moderately (2), or very much (3). Earlier studies identified the STAI as a validated and reliable instrument to measure the anxiety state of the parents, and it is validated in Dutch [24,32].

#### User Experience

Children will provide subjective assessments of the VR MRI app using a 0-100 graphic rating scale at T1. They are asked (1) to rate the amount of “fun” they had during the VR preparation (no fun to most fun); (2) to what extent they felt nausea as a result of experiencing the virtual world (no nausea to severe nausea/vomiting [VR condition only]); (3) how real the objects in the virtual world seemed (“completely fake” to “indistinguishable from a real object” [VR condition only]); and (4) to what extent they felt like they went into the virtual world while experiencing VR (“I did not feel like I went into the virtual world at all” to “I went completely into the virtual world” [VR condition only]). Adherence will also be addressed in the user experience questionnaire by asking children and parents how often and how long they used the VR preparation app.

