**Conclusions:**

The VR smartphone app is expected to significantly reduce pre- and periprocedural anxiety in pediatric patients undergoing an MRI scan. The VR app offers a realistic and child-friendly experience that can contribute to modern care. A smartphone version of the VR app has the advantage that children, and potentially their parents, can get habituated to the VR environment and noises in their own home environment and can do this VR MRI preparation as often and as long as needed.

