### Patient Recruitment and Procedure

For the prospective recruitment of patients, in concert with the radiologist, the planned MRIs will be scanned a month ahead for eligible patients. They will be informed about the study by mail or phone. If needed, they will be reminded by phone in the following weeks. Besides the reminder, this will help to overcome doubts, because the staff can answer questions or motivate the patients to participate.

All participants will receive an invitation, information folders, and an informed consent form. Participation is not obligatory, and all data will be anonymized. Parents of all the patients will be asked to sign informed consent. Children aged 12-14 years will also be asked to provide informed assent themselves. Patients aged younger than 12 years will give their verbal permission.

After receiving signed informed consent, the participants will be stratified by the type of MRI scan (head or body scan). Then, they will be randomly assigned to the VR group (n=64) or the CAU group (n=64).

The children assigned to the VR group will receive Google cardboard–like VR glasses and instructions on how to download the VR app on their phone and use the VR intervention at home. They will receive a log-in code to use the smartphone VR app. Adherence will be promoted by giving the participants detailed information about the purpose of the study and how to use the VR preparation app and explaining how they can get help from the contact support staff if there are difficulties with the app or VR glasses.

The allocation sequence was executed by a researcher who is not involved in the assessment phase. The psychologist who assesses the child’s anxiety state is blinded to the group assignment. This way, blinding for the treatment allocation will be guaranteed. Parents and children in both groups will be asked not to discuss their treatment allocation with the nurse, radiologist, or research psychologist.

Questionnaires will be assessed at the following time points: (1) T1, the weeks before the MRI scan (at home); (2) T2, the day of the MRI scan, before the procedure will start (in the waiting room); and (3) T3, right after the MRI scan (in the waiting room). The T3 questionnaires will retrospectively assess the child’s experience during the MRI scan. In this way, we can measure the anxiety during the MRI scan without the interruption of the procedure.

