### Strengths and Limitations

This study design has both strengths and limitations. A strength of this study is the RCT design and the multiple informant assessment of anxiety in children before and during the MRI scan. Most of the current preparation materials for children undergoing an MRI scan involve verbal explanation. The use of VR combines verbal explanation with visual information that can be beneficial for younger children or children who do not speak or understand the language. Additionally, the use of mobile phone–based VR creates the possibility to prepare children in their own time, at their own pace, and in the comfort of their own home. It also alleviates the personnel and space demands imposed by mock-scanner preparation. Due to the use of a smartphone-based VR experience that can be used at home, we can reduce the costs associated with using a tethered VR experience. The app presents a typical MRI room and thus can be used in any hospital without adjustments. Moreover, the app is designed to be easily localized to other languages. Furthermore, due to the use of 3D models instead of 360-degree video recordings, adjustments and adding or subtracting certain elements can be easily and cheaply done.

A limitation is that although we ask participants in the user experience questionnaire how often and for how long they have used the VR preparation app, we do not have more accurate measures of VR use. In addition, as the VR intervention is designed to be used at home in an environment that is comfortable for a child, we do not have information if the children used the VR MRI app with enough attention. The smartphone used by each child varies greatly in screen quality, size, and processing power. These differences might influence the VR experience, its image quality, and ultimately, the immersivity of the VR. Another limitation is that only children who do not need general anesthesia during the MRI scan are included, thereby potentially excluding the most highly anxious children. This may limit the generalizability of this study to children with less severe levels of anxiety. If this study shows that the VR MRI preparation app is efficacious, it would be important to study whether VR preparation can also reduce the need for anesthesia.

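### App use is asked about in the T1 questionnaire, before the preparation period has closed, so any later use goes unrecorded and the trial's only exposure measure can run low

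*Protocol article*

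**What the plan says.** Four places in the protocol article bear on this.

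- **User Experience (Outcome Measures).** The opening sentence fixes the time point: "Children will provide subjective assessments of the VR MRI app using a 0-100 graphic rating scale at T1". The section lists ratings of fun, nausea, realism and presence. It then says that adherence is covered in the same questionnaire, by "asking children and parents how often and how long they used the VR preparation app". No other time point is given for these items.
- **Patient Recruitment and Procedure.** The first time point is defined as "T1, the weeks before the MRI scan (at home"; the next contact is "T2, the day of the MRI scan, before the procedure will start (in the waiting room".
- **Abstract, Conclusions.** Children "can do this VR MRI preparation as often and as long as needed". The Introduction describes home use in similar open-ended terms. Neither place, nor any other, gives a date after which the app is closed or should no longer be used.
- **Strengths and Limitations.** Apart from the self-reported frequency and duration, "we do not have more accurate measures of VR use".

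**The concern.** The intervention is delivered at home without study staff, so the amount of preparation each child receives is left to the family. The usage questions are the only record of it. A measure of total exposure needs to be taken when exposure has ended. As written, it is taken at a point when the child may still go on to use the app, and sessions shortly before the scan are the ones most exposed to being missed.

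Two things depend on this record. One is the reported adherence of the VR group. The other is the reading of a null result: usage data are the only means of distinguishing an app that was hardly used from one that was used and did not help. The nausea rating has the same limitation, since it cannot cover sessions that follow the form.

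**Working it through.** The article attaches no figure to this point, so the check is mainly a comparison of timings.

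1. **When the exposure question is asked.** The User Experience section puts the child's ratings at T1 and the usage items in that questionnaire. Patient Recruitment and Procedure puts T1 at home in the weeks before the scan.
2. **When exposure ends.** The Abstract and Introduction allow use without limit of number or duration, and no stop date or lock-out is stated. The natural reading is that use may continue until the family leaves for the scan. This is an inference from the absence of a stop rule.
3. **Whether a later record exists.** T2 and T3 are described as anxiety assessments, and the text assigns no usage item to either. Strengths and Limitations says that nothing more accurate than the questionnaire is available.
4. **Direction of the error.** Write total use as U = B + A, where B is use before the T1 form is completed and A is use after it. The form can record only B. The error from timing is B − U = −A, which is zero or negative and never positive. Recall error comes on top and may go either way.
5. **Size of the error.** The missed share is A/U. The article gives neither the day on which T1 is completed nor the pattern of use over time, so A/U cannot be computed. It is 0 if the last session precedes the form, and grows with the gap between form and scan and with any increase in use as the scan approaches. The gap differs between families, so the shortfall does too.
6. **Effect on the planned analyses.** The Statistical Analysis Overview analyses children as randomized, whatever care they received. The Secondary Study Parameter(s) section treats user experience descriptively, and app use is not among the predictors listed for the exploratory regressions. The primary estimate therefore does not involve the usage data.
7. **Effect on the sample size.** The stated 128 rests on d = 0.5, two-sided α = .05 and power .80. An exact two-sample t-test gives 63.77, hence 64 per group and 128 in total, as stated. Adherence is not an input, so moving the usage items changes nothing here.

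**The case against.** The strongest reply is that T1 is a window and not a fixed early day. Nothing in the article prevents families from completing the form in the last days before the scan, when little use remains. The sentence on adherence does not itself name T1, and it adds parents as respondents, whereas the T1 sentence speaks only of children. Figure 2, which lists the instruments by time point, is not available in the text reviewed. No planned inference uses the data, and the article already concedes that use is measured imprecisely. Asking about VR at home also keeps the subject away from the waiting room where the blinded assessor works, and ratings of realism or fun given after a real scan could be coloured by it.

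Most of this stands, and it limits the point. The size is unknown and may be small. The T1 timing of the usage items follows from the questionnaire they sit in. The experience ratings are reasonably placed at T1. What does not stand is that the conceded limitation covers the matter: it speaks of the accuracy of self-report and of attention, and does not mention that the question precedes the end of use.

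Three stronger readings are tempting but unsupported.

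- A reader might infer that a child who first opens the app after T1 is recorded as a non-user. No such coding is described, and the experience items presuppose that the app has already been used.
- A reader might attach a percentage to the missed use by assuming even use over the window. That only restates the assumption, because the article gives no completion date and no usage pattern.
- A reader might infer that the CBCL, also collected at T1 and used as a covariate, is contaminated by the intervention. It is a parent report on the preceding 6 months, and nothing in the article suggests that an app of about 5 minutes would shift it.

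**Conclusion.** The point holds as a minor flaw in the timing of one measure. As the article is written, use between the T1 form and the scan is not recorded, so timing biases the only exposure measure downward by an amount that cannot be determined and could be close to nil. This rests on two readings of the text: that the usage items share the T1 timing of their questionnaire, and that use may continue up to the scan because no stop date is given.

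A reader might go further and conclude that the treatment comparison is compromised. It is not: the primary analysis is by intention to treat and does not use adherence. The loss is confined to the description of adherence, the coverage of nausea in later sessions, and the interpretation of a null result.

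**What to change.** - Keep the ratings of fun, nausea, realism and presence at T1.
- Ask, or repeat, the how-often and how-long items after the T3 anxiety ratings are complete, together with any nausea in sessions after T1. Use an online or sealed form that neither the blinded psychologist nor the staff sees.
- Record the date on which the T1 form was completed, so that the gap to the scan is known for each child.

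The cost is one or two extra items on the scan day. The sample size, error rate and primary analysis are unchanged. If Figure 2 or the full protocol already places the usage items later, a clarifying phrase in the User Experience section is enough. The article expected recruitment to end in December 2022. If data collection is over, adherence should be reported as use up to the T1 form, with the form-to-scan interval where dates exist.
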